### Statistical Considerations

Randomization of 51 SDHOs with an average cluster size of 40 individuals with diabetes at baseline will provide 90% power (2α=0.05) to detect an absolute mean HbA_1c_ difference of 0.5%. A change of 0.5% in HbA_1c_ is considered clinically meaningful [26]. Intracluster correlation coefficients of 0.05 for HbA_1c_ are assumed. By assuming a 10% dropout rate in our study, the sample size calculation indicated that a total of 1540 participants will be required to be recruited in both arms, with 770 in each group (Figure 2).

The analysis of change in HbA_1c_ between baseline and the end of study (primary end point) will be performed using a linear mixed model including treatment arm and baseline HbA_1c_ as fixed effects as well as SDHO as a random effect to account for clustering of individuals by village. In case of baseline imbalances between the 2 arms at the cluster or individual level, unbalanced characteristics will be added to the models as a sensitivity analysis. The same approach will be applied for continuous secondary end points.

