## Results

The study was funded by the Medical Research Council, United Kingdom in April 2018 with additional funding received from Medical Research Council and Imperial College London in September 2022. We had to delay the recruitment of the participants into the trial between the period 2020-2021 due to the unprecedented COVID-19 pandemic. As of May 2024, we have enrolled 1599 patients with type 2 diabetes, who are managed and followed up by community nurses at 51 SDHOs. Final data analysis and results are expected to be published in the first quarter of 2025.

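### The sample-size paragraph gives two incompatible sizes for the same 51-SDHO design: 90% power is tied to 40 patients per SDHO (2040), but the stated requirement is 1540

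*Protocol article*

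**What the plan says.** All the planning figures stand in one paragraph of the protocol article (Methods, Statistical Considerations). It opens with the power claim: "Randomization of 51 SDHOs with an average cluster size of 40 individuals with diabetes at baseline will provide 90% power", at two-sided 0.05, "to detect an absolute mean HbA_1c_ difference of 0.5" percentage points. On clustering it says: "Intracluster correlation coefficients of 0.05 for HbA_1c_ are assumed". After allowing for 10% dropout it concludes that "a total of 1540 participants will be required to be recruited in both arms, with 770 in each group".

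The Study Design section under Objective 2 repeats 51 SDHOs, randomized 1:1. The Results section says that, as of May 2024, "we have enrolled 1599 patients with type 2 diabetes", at 51 SDHOs. The article gives no SD for HbA1c, and no other section relates the 40 per SDHO to the 1540.

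**The concern.** The 40 per SDHO and the 1540 both describe patients at entry, for the same 51 clusters, so their product and total should agree. They differ by 500 patients. A reader cannot tell from the text which of the two designs carries the 90%.

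This power statement concerns the primary outcome. If the trial finds no difference in HbA1c, readers will weigh that result against a 90% chance of detecting 0.5, and that figure is attached to a cluster size that is not the trial's own.

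**Working it through.** **Inputs from the document.** 51 SDHOs; average 40 per SDHO at baseline; power 90%; two-sided 0.05; difference 0.5; intracluster correlation (ICC) 0.05; dropout 10%; 1540 to recruit; 1599 enrolled.

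**Assumptions made here.** Clusters split 25 and 26, equal cluster sizes, normal approximation. The SD is not stated, so it is solved for or varied.

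**Step 1: try to reproduce 1540.**
- 51 × 40 = 2040, and 2040 / 1540 = 1.32.
- If 2040 is before dropout: 2040 × 0.9 = 1836 analysed (36 per SDHO).
- If 2040 is after dropout: 2040 / 0.9 = 2267 to recruit.
- From the other side: 1540 / 51 = 30.2 per SDHO recruited, and 1540 × 0.9 = 1386, or 27.2 per SDHO analysed.
- At 40 per SDHO, 1540 would need 1540 / 40 = 38.5 SDHOs.
- Enrolled: 1599 / 51 = 31.4 per SDHO, or 28.2 after 10% dropout.

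The figure of 1540 is not reproduced under any of these readings.

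**Step 2: how much information is at stake.** Design effect DE = 1 + (m − 1) × 0.05; effective sample size = 51 × m / DE.

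| Patients per SDHO (m) | DE | Effective sample size |
|---|---|---|
| 40 | 2.95 | 691 |
| 30.2 (1540) | 2.46 | 626 |
| 27.2 (1540 less 10%) | 2.31 | 600 |

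The effective size falls by 9% (691 to 626), or by 13% after dropout (691 to 600).

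**Step 3: the SD that each reading implies.** SE = SD × √[(DE / m) × (1/25 + 1/26)]. Power of 90% needs 0.5 / SE = 1.960 + 1.282 = 3.242, so SE = 0.1543.
- m = 40: √(0.07375 × 0.07846) = 0.0761, so SD = 0.1543 / 0.0761 = 2.03.
- m = 36 (the 40 taken as before dropout): SD = 1.99.
- m = 27.2: √(0.08496 × 0.07846) = 0.0816, so SD = 0.1543 / 0.0816 = 1.89.

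The two statements therefore imply different SDs if each is meant to give exactly 90%. With a t reference distribution (49 degrees of freedom) the SDs at m = 40 and m = 27.2 become 1.99 and 1.85; the powers in Step 4 do not change.

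**Step 4: power for the real size if 90% was exact for 51 × 40 (SD 2.03).** Power = Φ(0.5 / SE − 1.96). The difference detectable with 90% power is 0.5 × √(691 / effective size).

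| Design | Power | Difference detectable with 90% power |
|---|---|---|
| 51 × 40 | 90.0% | 0.50 |
| 1540 | 87.0% | 0.53 |
| 1540 less 10% | 85.5% | 0.54 |
| 1599 | 87.4% | 0.52 |
| 1599 less 10% | 86.1% | 0.53 |

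If the 40 was already meant before dropout (SD 1.99), 1540 less 10% gives 86.7%.

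**Step 5: power at 1540 less 10% (27.2 per SDHO) over a range of SDs.** 98.3% at SD 1.5, 92.5% at 1.8, 90.0% at 1.89, 86.5% at 2.0, 79.5% at 2.2.

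**The case against.** One can grant the arithmetic and still argue that little follows from it.

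- **A loss of power is not shown.** With no SD stated, 1540 less 10% still reaches 90% if the SD was about 1.89 or less. The 85.5% rests on an SD solved from one of the two disputed statements. This stands.
- **The model adjusts for baseline HbA1c.** If the SD of 2.03 is unadjusted, an assumed baseline-to-endpoint correlation of 0.4 reduces it to 2.03 × √(1 − 0.16) = 1.86. That is below 1.89, so power exceeds 90%. The document does not say whether its SD is adjusted. This stands too, and it rules out simply replacing 90% with 86%.
- **The head-count gap exaggerates the effect.** The design behind the claim is about one third larger than 1540 (28% larger than the 1599 enrolled), but the clusters are unchanged and the effective size falls by only 9% to 13%. This stands.
- **An article may leave the SD to the full protocol, and Figure 2, cited with the 1540, is not available here.** Both are fair. The missing SD is not a defect in its own right. But neither a figure nor a fuller document can make 51 × 40 equal 1540 in this text.

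A reader might also notice that 1540 = 1.1 × 35 × 40 and infer that a 35-cluster calculation was carried over. Nothing in the document mentions 35 clusters, and the point does not need that explanation.

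**Conclusion.** Wrong as written. One paragraph gives 2040 and 1540 for the same 51 SDHOs, no dropout adjustment links them, and enrolment of 1599 is close to the second and well short of the first. The 90% is therefore attached to a cluster size that the trial neither targets in its total nor had reached by May 2024.

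The consequence is modest. If 90% was exact for 51 × 40, the loss is about 3 points at 1540 and 4.5 points after dropout. This rests on ICC 0.05, equal cluster sizes, a 25/26 split and an implied SD of 2.03. If the assumed SD was about 1.89 or less, there is no shortfall against 90%.

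A reader might infer that the trial is underpowered. The document does not support that: without the SD, one cannot say on which side of 90% the recruited design falls. What is established is the contradiction, which leaves the stated power unverifiable for the design being run.

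**What to change.** Rewrite the paragraph so that the clusters, the cluster size and the total agree:

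1. Say which figure the calculation used, and reconcile 40 per SDHO with 1540.
2. State the assumed HbA1c SD, and whether it is adjusted for baseline.
3. Restate the power, or the difference detectable with 90% power, for 51 SDHOs at the size recruited: about 30 to 31 recruited and 27 to 28 analysed per SDHO.

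The cost is one paragraph of wording. No extra patients and no change to conduct or to the primary analysis are needed. The only downside is that the stated power may become slightly less favourable. The change is best made before the primary result is interpreted.

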**Methods:**

A pragmatic, type 2 hybrid effectiveness or implementation, parallel-group cluster randomized controlled trial of 12 months duration and involving 51 subdistrict health offices in rural communities of Kamphaeng Phet province, Thailand, will be conducted. The intervention arm will receive the SMARThealth Diabetes program, including workforce restructuring, clinical decision support system, and continuous performance monitoring, while the control arm will continue with usual practice. Data will be collected using the SMARThealth platform and will be stored on a server in Thailand. The primary outcome measure will be the change in mean hemoglobin A_1c_ (HbA_1c_) measured at randomization and 12 months from randomization between the intervention and control clusters. Secondary outcomes will include the difference in change in albuminuria status, estimated glomerular filtration rate, systolic blood pressure, and low-density lipoprotein cholesterol level. The analysis for change in HbA_1c_ between baseline and end of study will be performed using linear mixed models. Any imbalances between the 2 arms will be addressed by sensitivity analyses. Additionally, a mixed methods process evaluation will be conducted to assess the implementation process, that will include in-depth interviews and focus group discussions, in addition to the quantitative data collected during the implementation process. The qualitative data will be thematically analyzed to explore factors that promote or inhibit the implementation and maintenance of the program.

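### Beyond the baseline value of the outcome, adjustment covariates are chosen by observed imbalance and used only in a sensitivity analysis; a short prognostic set should be named in advance

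*Protocol article*

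**What the plan says.** Under Statistical Considerations, the primary analysis of change in HbA1c is a "linear mixed model including treatment arm and baseline HbA_1c_ as fixed effects as well as SDHO as a random effect". Baseline HbA1c is therefore in the model whether or not the arms are balanced on it.

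Other characteristics are handled conditionally: "In case of baseline imbalances between the 2 arms at the cluster or individual level", then "unbalanced characteristics will be added to the models as a sensitivity analysis". The Methods paragraph of the abstract says the same: "Any imbalances between the 2 arms will be addressed by sensitivity analyses". The rule also covers other outcomes: "The same approach will be applied for continuous secondary end points".

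The Timeline section gives the order of events. SDHOs are randomized first, nurses in the intervention SDHOs are then trained, and community nurses then invite patients. Under Inclusion Criteria, patients may have known diabetes or may be identified at initial screening by those same nurses.

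**The concern.** For every covariate except the baseline outcome value, the observed arm difference decides whether it is used. Two properties of a covariate matter for the treatment estimate: how far it is shifted between arms and how strongly it predicts the outcome. The distortion in an unadjusted estimate is the product of the two. A rule that looks only at the shift can add a covariate unrelated to HbA1c change and pass over a strong predictor whose shift is moderate.

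With concealed individual recruitment, such shifts would be chance. Here the recruiters know the allocation, and in one arm they have had extra diabetes training. The case mix, for example known versus newly identified diabetes, could differ systematically. Beyond baseline HbA1c, the only stated response is a conditional sensitivity model whose content is settled after the baseline data are seen. At stake are some precision and some protection against measured recruitment differences, both obtainable from baseline data the trial already collects.

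**Working it through.** **Inputs from Statistical Considerations.** "Randomization of 51 SDHOs with an average cluster size of 40 individuals with diabetes at baseline"; "90% power (2α=0.05) to detect an absolute mean HbA_1c_ difference of 0.5"%; "Intracluster correlation coefficients of 0.05 for HbA_1c_ are assumed"; 10% dropout; 1540 to be recruited, 770 per arm. Both m = 40 and m = 1540/51 = 30.2 are used below, because the section supports either. Completers: 1540 × 0.9 = 1386, or 693 per arm and 1386/51 = 27.2 per SDHO.

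**The plan's own figure.** No SD of HbA1c is given in the article, so 1540 can be neither confirmed nor refuted. Solving SD = 0.5 × √(n_eff/2) / (1.960 + 1.282), with n_eff = 693/design effect and design effect = 1 + (m − 1) × 0.05:

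| m | Design effect | n_eff per arm | Implied SD |
|---|---|---|---|
| 40 | 2.95 | 234.9 | 1.67 |
| 30.2 | 2.46 | 281.7 | 1.83 |

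SDs of 1.8 and 2.0 are assumed in step 3.

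**Step 1: how often chance alone adds a covariate.** Suppose k independent candidates are flagged at 5% (an assumption; the article states neither k nor a test). The chance of at least one flag is 1 − 0.95^k: 23% for k = 5, 40% for k = 10, 64% for k = 20. A null simulation (51 clusters, cluster-level analysis, 8000 runs per scenario) gave 22–23% for 5 candidates and 41% for 10. Type I error in that simulation (Monte Carlo standard error about 0.25 points):

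| Model | Type I error |
|---|---|
| Unadjusted | 5.1–5.4% |
| Covariates selected on imbalance | 4.5–4.9% |
| Prespecified covariates | 4.6–5.4% |

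So chance influences what the sensitivity model contains, but no inflation appeared. The simulation randomized clusters and did not model recruitment by staff who know the allocation.

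**Step 2: precision from a prespecified set.** The within-cluster share of the variance of a cluster mean is (1 − ICC)/(1 + (m − 1) × ICC): 0.95/2.95 = 32% at m = 40 and 0.95/2.46 = 39% at m = 30.2. Let the covariates explain a fraction R² of the remaining variance (assumed). The standard error is multiplied by √(1 − R² × share) if only individual-level variance is explained, and by √(1 − R²) if between-SDHO variance is explained equally.

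| R² | SE reduction, individual level only (m = 40; m = 30.2) | SE reduction, both levels |
|---|---|---|
| 5% | 0.8%; 1.0% | 2.5% |
| 10% | 1.6%; 1.9% | 5.1% |
| 20% | 3.3%; 3.9% | 10.6% |

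**Step 3: power.** With 1386 completers the design effect is 1 + 26.2 × 0.05 = 2.31, n_eff = 693/2.31 = 300 per arm, and the within-cluster share is 0.95/2.31 = 41%. The standard error is SD × √(2/300): 0.147 for SD 1.8 and 0.163 for SD 2.0. Power is Φ(0.5/SE − 1.96).

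| Assumed SD | No extra covariates | R² = 10%, individual level only | R² = 10%, both levels |
|---|---|---|---|
| 1.8 | 92.5% | 93.5% | 94.8% |
| 2.0 | 86.5% | 87.9% | 89.8% |

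**The case against.** The strongest defence is that a prespecified arm-plus-baseline model is a legitimate primary analysis and already contains the most obvious prognostic covariate. A reader might infer that all adjustment hinges on imbalance, that the primary test is chosen from the data, or that its error rate is inflated. The documents support none of these. Baseline HbA1c enters unconditionally, imbalance-triggered covariates are confined to a sensitivity analysis, and the null simulation showed no inflation. Nor does anything suggest that the sensitivity model would displace the primary one; the order between them is explicit.

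It is also fair that a definition of imbalance and a list of candidates may stand in an analysis plan or full protocol not shown here. Their absence from an article is no finding and is not held against the plan. But neither would change the criterion, which the article states affirmatively: selection would still follow shift rather than prognostic value.

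Two further objections stand in part. If recruitment makes imbalance systematic, looking at what actually shifted has some use, and a fixed list could miss that factor. And adjustment for measured covariates cannot remove selection on unmeasured ones, so the protection is partial. Newly identified diabetes depends on screening by nurses who, in one arm, have been trained, so that variable may itself be affected by allocation.

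**Conclusion.** The point holds in a limited form. Beyond the baseline outcome value, covariates are selected by imbalance and used only in a sensitivity analysis. That is weak practice in any trial, and more so where recruitment follows allocation. It does not invalidate the primary test.

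The benefit of changing it is modest. At an assumed 10% of remaining variance explained, the treatment-effect standard error falls by about 2% if only individual-level variance is explained, and by up to about 5% if between-SDHO variance is explained equally. In power this is 1 to 2.3 percentage points at an assumed SD of 1.8, and 1.4 to 3.3 points at 2.0. The R² and SD values are assumptions. Any bias from recruitment is not quantified, because the article gives neither the shifts nor the prognostic strengths, and it does not show that an imbalance has occurred.

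**What to change.** Before database lock, name a short set of prognostic baseline covariates and include them, with the baseline value of the outcome, in the primary model for HbA1c and for each continuous secondary end point. Candidates are age, sex and baseline glucose-lowering medication; the Timeline and Data Collection and Management sections say that demographics and current diabetes medication are collected. Known versus newly identified diabetes could be added if it is recorded, with the caveat that allocation may have influenced it. Add an SDHO-level factor only if it is already available; the article does not say that any, such as register size, is collected.

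Keep the arm-plus-baseline model as the sensitivity analysis, and delete the rule that selects covariates on observed imbalance. Baseline differences can still be described by arm.

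The cost is wording and a few degrees of freedom, which calls for a short list with 51 clusters, above all for SDHO-level terms. The Results section reports 1599 patients enrolled as of May 2024, so recruitment can no longer be redesigned and the analysis is where this can still be addressed.

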**Figure 2 figure2:**
[figure not shown]
Randomization and sampling based on the SDHOs. SDHO: subdistrict health office.

### Data Collection and Management

Data collection will commence at baseline (0 months; randomization) and will be conducted quarterly at 3, 6, 9, and 12 months after randomization by community nurses. All data will be captured on tablet devices using the SMARThealth app adapted for the clinical research forms (CRFs). The CRFs collect information on anthropometric measurements, medical history, and current medication for hypertension, diabetes, and hyperlipidemia, in addition to laboratory test results. These CRFs will be completed at months 0, 3, 6, 9, and 12. The primary outcome variable (HbA_1c_) and other laboratory tests will only be recorded at months 0, 6, and 12. Data will be deidentified, saved, and stored in a secure server located in Bangkok, Thailand. Published, validated questionnaires are used in the CRFs and tested using the SMARThealth platform before data collection. About 10% of all CRFs will be checked for accuracy against source data by the project team.

SMARThealth platform will be used for digitally collecting all baseline and outcome data. Data access will be restricted to delegated study staff and will require multifactor identification with a digital log kept of all logins. The project manager and data managers will be responsible for data quality. The project manager will ensure quality by interacting periodically with community nurses and checking for completeness of data, and data validation.

### Confidentiality

Participant confidentiality will be maintained throughout the study. Each participant in the study will be assigned a 10-digit unique alphanumeric patient ID. The first 2 digits are the district code, the following 5 digits are the SDHO code, and the last 3 digits indicate the individual patient ID. This unique ID ensures that their personal identifiers remain anonymized throughout the research process.

Our data management system employs 3 robust security layers to safeguard patient data. First, password protection is implemented to regulate access, preventing unauthorized usage by individuals. Second, local data protection measures, including encrypted data communication and role-based access, are implemented to ensure the security of the locally stored data at the device level. Finally, at the server level, additional measures such as firewall protection, reliable maintenance, monitoring, and support services are implemented to safeguard the database.

### Process Evaluation

A detailed awareness of local contextual factors will be undertaken to understand the impact of SMARThealth and barriers to its implementation and scale-up. The process evaluation will be designed in line with recommendations by the UK Medical Research Council in its “guidelines for developing and evaluating complex interventions” [27,28]. Evaluation data, data collected during intervention delivery, and data collected through qualitative methods will be used to investigate the process evaluation framework that includes identifying factors that promote or inhibit the implementation and maintenance of the program [29]. A maximum variation sampling technique will ensure diverse opinions are captured from participants and health care workers. The process evaluation will be informed by normalization process theory (NPT) [30] to assess the extent to which the new system fits within the normal processes of the current service provision in the villages and SDHOs. The 4 main concepts of NPT namely, coherence, cognitive participation, collective action, and reflective monitoring will be identified in the process of implementation of the SMARThealth diabetes program in the intervention SDHOs.

Key evaluation areas that the study will explore are: (1) how the health workers use the intervention, (2) what effects the intervention might have on doctor practices, and (3) participant experiences of receiving the intervention.

Qualitative data will be collected using semistructured, in-depth interviews and focused group discussions [31]. NPT will inform the semistructured interview guides and will also be used as a framework for analyzing the data. All interviews and group discussions will be audio-recorded, and then transcribed verbatim. The qualitative data will be thematically analyzed (from codes to categories and finally themes) to identify and interpret patterns and themes within the data. Data will be analyzed contemporaneously, and data collection will be stopped when thematic saturation is reached. Two researchers who are trained in qualitative methodology will be involved in coding the interview and FGD transcripts. In the event of a disagreement, a consensus meeting will be held with the principal investigator to reach an agreement on interpretation of the data. Intercoder reliability will be reported using qualitative assessments of agreement and consistency among the coders using processes described by O’Connor and Joffe [32]. Process evaluation data will be analyzed independently of the outcome evaluation data and then the 2 sets of data will be combined and triangulated to increase the reliability of the results.

